## 2. Materials and methods

The FoodACT study will comprise a multimethod, quasi-experimental inquiry into the existing school garden program GtB. RCTs are widely used in educational research to reduce bias in estimating the effects of the intervention [46]. RCT studies have previously shown health effects of school garden interventions [11]. However, when applied to school settings, RCTs necessitate a somewhat artificial (“unnatural”) intervention from outside the school system itself, which does not reflect how educational initiatives or programs are implemented, established, and scaled up in real life. In other words, RCT designs enable high internal validity regarding effects but often have low external pragmatic/ecological validity because the intervention investigated does not reflect real-life school practices well and often cannot be implemented long-term or scaled up in municipals and schools without significant alterations. The aim of the FoodAct study was to study the impacts of an already established school-garden program, namely the GtB program. This was chosen in order to ensure scalability and sustainable implementation of the intervention studied which is important for pragmatic validity or practical/political relevance of the study. The GtB program is implemented at the municipality level, which means that it is a political decision to financially prioritize whether the schools within the municipality get to participate in GtB or not. Randomizing which schools or classes would get to participate is thus not acceptable from a municipal perspective (in Denmark) making it impossible to recruit municipalities and hence schools to an RCT trial of this school garden program. We therefore chose a natural experiment approach [47–49] to evaluate the outcomes associated with participating in an already developed, established, and widely used school garden program in Denmark. Based on the practical nature of the GtB program, the study will be a non-randomized controlled natural experiment [44], drawing on various study designs through sub-studies (see Fig 3), which will be elaborated upon in the following sections.

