### 2.2 Recruitment and participants

The recruitment and enrollment of fourth grade pupils in the study was first initiated in September 2023 and ended in January 2024. Municipalities decide whether to offer the GtB program to schools within their district, which then sign up for the program on a yearly basis. All contact information for the schools will be provided by GtB. All contact information for the schools will be provided by GtB. School classes from public primary (non-private) schools that are signed up for the GtB program in 2024 but will not yet have started the program will be invited to participate in the intervention group via e-mail. Similarly, school classes who have not previously been and will not be enrolled in GtB in 2024 will be invited to participate in the control group via e-mail. The recruitment and inclusion of control classes will be based on similarity with the intervention schools regarding geographical proximity and average disposable income at the municipal level to enhance comparability between the intervention and control schools. First, a list will be comprised of municipalities that approximately match intervention municipalities on average disposable income (based on 2017 data from Statistics Denmark) [51] and are in the closest possible geographic proximity to the intervention municipality. For example, intervention schools located on the Danish Island of Funen will be matched with control schools in a different municipality on Funen but with a similar municipal average disposable income. Based on this list, public primary (non-private) schools within suitable control municipalities will be invited to participate, and an even distribution of school classes within the matched municipalities will be attempted. However, all schools indicating that they wish to participate will be enrolled in the study.

As part of the recruitment, teachers will be asked to provide all parents with written information about the study. Parents will subsequently be invited to provide electronic informed consent for their children’s participation. For SS2 and SS3, pupils will be asked to provide oral consent on the day of data collection. The recruitment process will be supported by general information available on the study project website [52]. By the end of data collection, all participating classes, including the control group, will receive a reimbursement equivalent to 200 EUR in recognition of their contribution.

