#### 2.4.5 Statistical analyses.

Linear mixed models will be applied to assess the intervention effects on FL, CCL, and SM [58]. Two-tailed tests with p-values below 0.05 will be considered statistically significant.

The analyses will account for the pupils’ nesting in their school classes by introducing school class as a random effect in the models. Intervention effects will be estimated through the inclusion of a group variable (intervention or control) and by adjusting for the outcome measure at baseline as well as confounders. Significantly better developments in these measures in the intervention group compared to the control group when adjusting for baseline level and confounders will be interpreted as a positive effect of the GtB program. Due to the lack of randomization, the analyses will be adjusted for known confounders such as gender, and SES. The analysis on the effect of GtB on FL will be further adjusted for participation in food and cooking classes during fourth grade or first semester of fifth grade. The analyses on the effect of GtB on FL and CCL will also be adjusted for age. Lastly, ICCs will be calculated by running the linear mixed models without the covariates to assess potential variation among school classes as fractions of the total variance. All analyses will be conducted using RStudio (version 1.4.1106; RStudio, Inc.) and IBM SPSS Statistics (version 29.0.1.0; IBM Corp.).

The models are expressed as follows:

$$\begin{array}{l} \text{Effect of GtB on FL:Endline FL }(\text{Y})=({\text{β}}_{0}+{\text{b}}_{\text{class}})+{\text{β}}_{1}\text{ FL baseline}+{\text{β}}_{2}*\text{int\_con}+{\text{β}}_{3}*\text{gender}+\\ {\text{β}}_{4}*\text{SES}+{\text{β}}_{5}*\text{age}+{\text{β}}_{6}\text{ food\_cooking\_class}+\text{ε} \end{array}$$

$$\begin{array}{l} \text{Effect of GtB on CCL:Endline CCL }(\text{Y})=({\text{β}}_{0}+{\text{b}}_{\text{class}})+{\text{β}}_{1}\text{ CCL baseline}+{\text{β}}_{2}*\text{int\_con}+\\ {\text{β}}_{3}*\text{gender}+{\text{β}}_{4}*\text{SES}+{\text{β}}_{5}*\text{age}+\text{ε} \end{array}$$

$$\begin{array}{l} \text{Effect of GtB on SM:Endline SM }(\text{Y})=({\text{β}}_{0}+{\text{b}}_{\text{class}})+{\text{β}}_{1}\text{ SM baseline}+{\text{β}}_{2}*\text{int\_con}+\\ {\text{β}}_{3}*\text{gender}+{\text{β}}_{4}*\text{SES}+\text{ε} \end{array}$$

Explanation for model concept for effects on FL, CCL and SM:

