To accommodate this limitation, we will attempt to ensure that the intervention and control schools are comparable in terms of average disposable income at the municipal level. The GtB school garden program has existed through 18 years and their practical experience with organizing, recruiting, and teaching pupils in the school gardens will be a strength of this study, as it secures feasibility and an institutional structure for sustained program implementation. The garden sessions are led by GtB’s own facilitators who hold a professional background in relevant fields, which ensures that the intervention is delivered similarly and with high quality across the different garden locations. The GtB program has previously been process evaluated using qualitative methods [78] and other researchers have investigated school subject integration within the GtB school gardens [79]. These findings have contributed to enhancing the program over the years, resulting in increased relevance for its target group.

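### SS1 fixes in advance that a significantly better adjusted endline score is a programme effect, but in self-selected groups a stable starting gap survives the baseline adjustment in part and can produce that result with no effect

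*Protocol article*

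**What the plan says.** In sub-study 1 (SS1), section 2.4.5 estimates the effect on food literacy (FL), climate change literacy (CCL) and school motivation (SM) with a linear mixed model for the endline score. It has a random intercept for class and a group term, and it works "by adjusting for the outcome measure at baseline as well as confounders". All three models adjust for gender and SES. Age is added for FL and CCL, and participation in food and cooking class for FL. The test rule is "Two-tailed tests with p-values below 0.05 will be considered statistically significant". A significantly better development in the intervention group "will be interpreted as a positive effect of the GtB program". The sentence attaches no condition on baseline balance or residual selection.

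Section 2 explains how exposure arises: "it is a political decision to financially prioritize whether the schools within the municipality get to participate in GtB or not". Section 2.2 adds the school's part, "which then sign up for the program on a yearly basis". Control schools are public schools in other municipalities, chosen for similar average income and proximity, in classes that have not been in the programme. Within that list participation is voluntary: "all schools indicating that they wish to participate will be enrolled in the study". The Discussion calls the lack of randomisation a central limitation and answers it by trying to make the schools "comparable in terms of average disposable income at the municipal level".

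**The concern.** The interpretation rule would be safe if the adjusted comparison removed every pre-existing difference between the groups. It need not. Schools whose municipality pays for a garden programme, and which then sign up, may already differ in food or climate teaching or in engagement. Nothing is matched on outcome level. Beyond baseline, pupil-level adjustment is limited to gender and SES, plus age for two outcomes.

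The baseline score is the main protection, but it is an imperfect measure of the stable level. The FL questionnaire was validated in older pupils and modified for this age group. The CCL instrument is new. Baseline and follow-up lie either side of a programme that runs from March to October. A within-group slope below 1 is therefore likely, and with such a slope the model removes only part of a stable gap. The rest appears in the group coefficient, which the rule reads as an effect.

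A larger sample does not cure this. The bias stays while the standard error falls, so better recruitment makes a false claim more likely. The results are meant to inform policy and funding, so taking selection for effect would matter.

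**Working it through.** **1. The plan's own figure.** Section 2.4.4 gives 25 classes per group, 18 pupils per class, ICC 0.046, power 0.80, two-sided 0.05 and three covariates. With J = 50 classes in total and df = 50 − 3 − 2 = 45:

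- SE = √(4·ICC/J + 4·(1 − ICC)/(J·n)) = √(4·0.046/50 + 4·0.954/900) = 0.0890
- Minimum detectable effect = (2.014 + 0.850) × 0.0890 = 0.255
- Interval: 0.255 ± 2.014 × 0.0890 = 0.076 to 0.434

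This reproduces the stated 0.255 [0.076, 0.434], so the same variance formula is used below.

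**2. Bias of the planned model.** Let there be no true effect. Let d0 (in SD) be a stable gap, present at both waves, that is left after gender, SES and the other covariates. Let b be the within-group slope of endline on baseline.

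- Group coefficient = endline gap − b × baseline gap = d0 − b·d0 = d0 × (1 − b)

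Sample size does not enter.

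**3. Standard error at the recruitment target.** Section 2.2 aims for 75 classes per group, so J = 150. I keep n = 18 from section 2.4.4 and assume that baseline explains b² of the variance at both levels.

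- Without baseline: √(4·0.046/150 + 4·0.954/2700) = 0.0514
- SE = 0.0514 × √(1 − b²) = 0.041, 0.037 and 0.031 for b = 0.6, 0.7 and 0.8

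**4. Chance of a significantly better result with no effect** (noncentral t, nominal 2.5%):

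| d0 (SD) | b = 0.6 | b = 0.7 | b = 0.8 |
|---|---|---|---|
| 0.05 | 7% | 6% | 5% |
| 0.1 | 16% | 13% | 9% |
| 0.2 | 49% | 37% | 25% |

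At d0 = 0.2 the spurious coefficients are 0.08, 0.06 and 0.04 SD. With about 21 pupils per class (1600/75) the last row becomes 52%, 39% and 27%. With d0 = −0.2 (n = 18) the same 49%, 37% and 25% become significantly worse results, and a false better result is almost impossible.

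**5. Simulation check.** The planned mixed model was simulated without the other covariates, with 1000 runs per setting, test–retest correlation 0.5 to 0.8, and class variance either fully stable or half specific to each wave. At 150 classes of 21 pupils the false better rate was 2–3% at d0 = 0, 5–10% at 0.05, 7–30% at 0.1 and 15–80% at 0.2. At 50 classes of 18 it was 8–32% at 0.2, which confirms that the larger sample raises the rate. The mean coefficient at d0 = 0.2 and correlation 0.7 was about 0.06 SD, as step 2 predicts.

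**6. The change score on the same data.** Its group coefficient was about 0, with two-sided rejection of 3–6.5%. That holds because the gap was made stable. If the groups instead regress to a common mean, the endline gap is b·d0. The planned model is then unbiased, and the change score is off by b·d0 − d0 = −d0 × (1 − b). The two estimates always differ by the baseline gap times (1 − b), so the study can compute the width of the range from its own data.

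**The case against.** The rule is narrower than a quick reading suggests. It covers only significantly better results, and only after adjustment for baseline and confounders. A reader might infer that any significant difference will be called an effect; the text does not say that.

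The safeguards are also more than income matching. Section 2.2 adds proximity and public schools only, and it excludes control classes with earlier programme exposure. Section 2.4.5 adjusts for pupil-level SES and gender expressly because randomisation is lacking. Only the gap left after all this counts. The design is labelled quasi-experimental, and section 2 speaks of outcomes associated with participation. All of this stands, but none of it conditions the interpretation sentence.

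A reader might also infer that the rule will often give false effects. The documents do not support that, because they give no starting difference, no sign for it and no slope. Frequent false claims need an unexplained gap of roughly 0.2 SD in favour of the intervention group.

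Nor is the planned model shown to be wrong. With two waves, the choice between baseline adjustment and change score rests on an assumption that cannot be tested. Requiring both to be significant would import the change score's opposite bias and could hide a real effect. Finally, a sensitivity analysis may stand in an analysis plan that is not shown, so its absence here is not the finding. The finding is the stated rule.

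**Conclusion.** The point holds as a criticism of one stated rule. Section 2.4.5 commits to a causal reading that the group formation in sections 2 and 2.2 does not support without a condition. The mechanism is certain: d0 × (1 − b) of a stable residual gap stays in the coefficient and does not shrink with recruitment.

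Its size is conditional. With no true effect, b between 0.6 and 0.8, 150 classes of 18 pupils and ICC 0.046, the false-claim rate is about 5–7% at 0.05 SD, 9–16% at 0.1 SD and 25–49% at 0.2 SD, against 2.5%. A wider range of assumptions gives wider ranges. If the intervention group starts lower, the bias can hide a benefit or suggest harm. Since d0 and b are unknown, these figures show what the rule permits and do not forecast what the study will find. The matter should be changed, because it governs what SS1 may conclude.

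**What to change.** 1. Keep the baseline-adjusted mixed model as the primary analysis.
2. Reword the sentence in section 2.4.5: a significantly better adjusted result is an adjusted association consistent with a programme effect, to be read together with the reported baseline group differences.
3. Report the same mixed model on the change score (endline minus baseline) as a sensitivity analysis for FL, CCL and SM. Present the two estimates as a range under two stated assumptions: the gap is stable (change score), or the groups regress to a common mean (baseline adjustment). Do not require both to be significant.

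The cost is one extra model per outcome on data already collected, one reworded sentence, and a more cautious conclusion when the two estimates differ.

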### 2.5 Sub-study 2: Physical activity and movement behavior in the school gardens

#### 2.5.1 Design.

A within-subject design will be applied for investigating whether, and to what extent, the pupils’ PA and acute SM are different in the school gardens compared to teaching as usual (i.e., classroom-based teaching). PA will be measured using accelerometry for two weeks out of which the pupils will attend the school garden one day. The pupils’ experience of basic psychological needs satisfaction, intrinsic motivation, and perception of the learning environment on school garden days and days with teaching as usual will be measured using an electronic survey distributed by a text-message to the parents on days they attend the school garden and on usual schooldays, in total seven days simultaneously with measuring PA.

#### 2.5.2 Outcome measures.

***Physical activity (PA):*** Will be measured with SENS motion^®^ accelerometers (SENS motion PULS pnr.A01.6, SENS Innovation, Copenhagen Denmark, 2024) [59]. The primary outcomes will be pupils’ PA levels, i.e., sedentary behaviour (SED), light-physical-activity (LPA), moderate-physical-activity (MPA), and moderate-to-vigorous PA (MVPA), as well as activity types (lying, sitting, standing, walking, cycling, and walking) measured in minutes per day. The data will be included in the analysis as scale data with information on minutes spent in the PA level categories and in the categories of activity types.

****Psychological needs satisfaction and intrinsic motivation during schooldays with and without school garden sessions******:** This will be measured using a 12-item instrument which measures the extent to which children experience intrinsic motivation/enjoyment (three items) and have their basic psychological needs for experiencing competence (three items), relatedness (three items), and autonomy (three items) satisfied as described by Self-Determination Theory and Basic Psychological Need Theory [54]. Responses to items are scored on a four-point Likert scale (one= Not at all true, two = Not very true, three= Sort of true, four = Very true) and will be included in the analysis as categorical data. The instrument has been developed for and pilot-tested in two previous school-based intervention studies [60,61]. The items for measuring experiences of intrinsic motivation, competence, and autonomy are based on the Interest/Enjoyment, Perceived Choice/Autonomy, and Perceived Competence sub-scales of the Intrinsic Motivation Inventory (IMI) [62]. The items for measuring experiences of relatedness are inspired by the relatedness satisfaction subscales of Basic Psychological Need Satisfaction Scales, Basic Psychological Need Satisfaction and Frustration Scale (BPNSNF) [63] and the Psychological Need States in Sport Scale (PNSS) [64].

****Learning environment perception:**** Will be measured with the Learning Rating Scale (LRS). It is a four-item scale answering on a 10 centimetre visual analogue scale and evaluates the pupils’ view of how much they learn at school, how well they are getting along, and whether the teaching methods suit them [65]. The 10 cm visual analogue scale ranges from zero to 100, not visible to the participant. The place where the participant chooses to put their answer provides a number from zero to100, e.g., 46. The data will be included in the analysis as scale data.

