The aim of the FoodACT study is to investigate the impact and mechanisms of an already established school garden program on children’s FL, CCL, SM, and PA. The Garden to Bellies (GtB) school garden program has been operational in Denmark since 2006. The program is chosen as a natural experiment intervention in the FoodACT study since it is already widely applied in Denmark and therefore feasible with potential for scalability in a real-world setting [43]. Identifying the impacts of interventions that are feasible, implementable, and scalable in real-world settings, such as GtB, will result in evidence that can have a high societal impact and relevance (i.e., ecological validity) [44]. However, when assessing the effects of a school program that operates independently of the study, it becomes impractical to employ the attributes of a randomized controlled trial (RCT) design, such as randomizing pupils into intervention or control groups or exercising greater control over the activities of both implementers and pupils. Despite the challenges posed by this complexity, and the need to eliminate biases through an appropriate study design, the evaluation of real-world natural experiment interventions offers a distinct advantage in terms of opportunistic evidence, flexibility, and investigation of delivery at larger scales [45]. The purpose of this paper is therefore to present and discuss the hypotheses, study designs, data collection procedures, measures, and analytical strategies, that will be applied in the FoodACT study.

The study will investigate two hypotheses which are supplemented by a process evaluation of implementation and mechanisms. The testing of the two hypotheses and the process evaluation will be investigated in three sub-studies, as illustrated in Figs 1 and 2 and described in Table 1.

**Table 1 pone.0320574.t001:** Hypothesis and secondary aim of the FoodACT protocol.

Hypothesis 1	Pupils participating in the school garden program develop higher levels of FL, CCL, and SM compared to pupils that undergo teaching as usual.	Sub-study 1 (SS1)
Hypothesis 2	The pupils’ PA levels are higher and involve different patterns of movement on school garden days compared to usual school days.	Sub-study 2 (SS2)
Process evaluation research question	Was the GtB program implemented as intended, and how does underlying mechanisms operating in the school gardens relate to the potential effects on FL and CCL?	Sub-study 3 (SS3)

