#### 2.4.4 Sample size.

Based on the recruitment target of previous similar studies in a Danish school setting, power calculations were conducted using 25 school classes with an average of 18 pupils per class in each group to calculate a minimum detectable effect size. This approach was chosen due to the limited existing research on the effects of school gardens on the chosen outcomes of this study. Power calculations were completed in the R package PowerUpR. In the calculations, the clustered nature of data with pupils nested in classes was considered, conventional levels of statistical power (0.8), and 2-tailed level significance (0.05) were applied. An intraclass correlation (ICC) of 0.046 was used based on a similar dataset of pupils from a Danish study on EOtC [56]. Adjustments for three covariates were also included in the calculation. Power calculations show that with this sample, the minimum detectable effect size of Cohen’s d would be 0.255, 95% CI [0.076,0.434]. This effect size is substantially smaller compared to what has been found in another less intensive school-based intervention aiming to increase pupils’ FL [57]. This suggests that even though the intended recruitment level is not achieved, or a high drop-out rate becomes prevalent, the study will be sufficiently powered.

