#### 2.5.5 Statistical analysis.

All analysis will be conducted in the statistical program RStudio (version 1.4.1106; RStudio, Inc.) [68]. Linear mixed models taking into account the clustered nature of data with days clustered in pupils clustered in classes will be conducted to test differences between the pupils’ PA, basic psychological needs satisfaction, and intrinsic motivation on days with the school garden program and usual school days. Two-tailed tests with p-values below 0.05 will be considered statistically significant. All analyses will be adjusted for gender, and SES. Additionally, analyses adjusted for physical education, size of school garden and transport to/from the school garden will be applied in relevant sub-analysis.

The models are expressed as follows:

$$\begin{array}{l} Acute\;SM:\\ \text{Mean acute SM}(\text{Y})=({\text{β}}_{0}+{\text{b}}_{\text{class}}+{\text{b}}_{\text{id}})+{\text{β}}_{1}*\text{school\_schoolgarden}+{\text{β}}_{2}*\text{gender}+{\text{β}}_{3}*\text{SES}+\text{ε} \end{array}$$

$$\begin{array}{l} Acute\;PA:\\ \text{Mean PA}(\text{Y})=({\text{β}}_{0}+{\text{b}}_{\text{class}}+{\text{b}}_{\text{id}})+{\text{β}}_{1}*\text{school\_schoolgarden}+{\text{β}}_{2}*\text{gender}+{\text{β}}_{3}*\text{SES}+{\text{β}}_{4}*\text{weather}+\text{ε} \end{array}$$

Explanation for model concept for effects on acute SM and PA:

Y = The dependent variable (outcome) being analyzed, such as a score after the intervention.β_0_ +b_class_ + b_id_ = The intercept of the model.β_0_ represents the fixed intercept, which is the expected value of Y when all predictor variables are set to zero.β_class_ is the random intercept for class, which accounts for potential similarities among pupils within the same class.β_id_ is random intercept for individuals within each class, capturing within-class variation.β_1_ * school_schoolgarden = The effect of being in a school garden versus a regular school day.β_1_ represents the difference in Y between school garden days and school days.β_2_ * gender = The effect of gender.Gender is coded as a categorical variable (0 = boy, 1 = girl, 2 = other), β_3_ represents the difference in Y (outcome) between genders (boy, girl or other).β_3*_ SES = The effect of socioeconomic status (SES).β_3_ shows how changes in SES impact Y.β_4*_ weather = the effect of weather.β_4_ shows how weather conditions influence Y.ε = The residual error term, capturing unexplained variation in Y.

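### Sub-study 2 tests nine distinct co-equal primary physical activity outcomes, two of them overlapping, each at an unadjusted 0.05 under a single hypothesis

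*Protocol article*

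**What the plan says.** **Sub-study 2.** Hypothesis 2 (Table 1, section 1) is a single statement in two parts: "The pupils’ PA levels are higher and involve different patterns of movement on school garden days compared to usual school days". Section 2.5.2 sets the outcomes for it: "The primary outcomes will be pupils’ PA levels, i.e., sedentary behaviour (SED), light-physical-activity (LPA), moderate-physical-activity (MPA), and moderate-to-vigorous PA (MVPA"), and continues "as well as activity types (lying, sitting, standing, walking, cycling, and walking) measured in minutes per day". No entry is ranked above another. Section 2.5.5 gives one model form for physical activity (PA) and one criterion: "Two-tailed tests with p-values below 0.05 will be considered statistically significant". It mentions no adjustment for the number of outcomes.

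**Sub-study 1.** Hypothesis 1 joins three outcomes, food literacy (FL), climate change literacy (CCL) and school motivation (SM): "Pupils participating in the school garden program develop higher levels of FL, CCL, and SM compared to pupils that undergo teaching as usual". Section 2.4.5 writes a separate mixed model for each, sets the same 0.05 threshold, and gives the reading rule: "Significantly better developments in these measures in the intervention group compared to the control group when adjusting for baseline level and confounders" will count as a positive effect of the program. The sample size calculation in section 2.4.4 treats one test: "conventional levels of statistical power (0.8), and 2-tailed level significance (0.05) were applied".

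**The concern.** When many outcomes share the label primary and each is judged at 0.05, the error rate for the hypothesis they jointly serve is no longer 5%. Any one of nine significant results could be presented as a primary finding in support of Hypothesis 2, and the text gives no rule for reading a mixed set of results.

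Two features of the list make this worse:
- The repeated activity type leaves the primary set undefined. The second walking may be a plain duplicate or may stand in place of another type, and the article does not say which.
- MPA minutes form part of MVPA minutes, so one difference in MPA can produce two primary findings.

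In Sub-study 1 the question is narrower. A hypothesis worded for three outcomes together is tested by three separate models, and the text does not say what follows if only one or two succeed.

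**Working it through.** **1. Count of primary PA outcomes (section 2.5.2).** Intensity: sedentary, light, MPA, MVPA = 4. Activity types: lying, sitting, standing, walking, cycling, walking = 6 entries, 5 distinct. Total: 10 entries, 9 distinct.

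**2. Family-wise error for Sub-study 2.** With k independent tests at 0.05, the chance of at least one false positive is 1 − 0.95^k.
- k = 9: 1 − 0.95^9 = 0.370
- k = 10 (if the repeated entry stands for another type): 1 − 0.95^10 = 0.401
- k = 8 (MPA/MVPA overlap removed, nothing else changed): 1 − 0.95^8 = 0.337

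Cleaning the list alone therefore does not solve the problem.

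The article gives no correlations between the outcomes, so a range was simulated. Test statistics were standard normal with a common correlation r, and each was compared with ±1.96.

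| Assumed r | 9 outcomes, any false positive |
|---|---|
| 0 | 37.0% |
| 0.3 | 32.6% |
| 0.5 | 26.8% |
| 0.7 | 20.1% |
| 0.9 | 12.4% |

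Equal positive correlation is a simplification, because minutes within a day trade off against each other. A second simulation used assumed variances, a fixed total of minutes and MPA overlapping MVPA. It gave 28.5% for the nine outcomes, just above the r = 0.5 value. For jointly normal two-sided tests, independence is the worst case (Šidák's inequality), so 37% is a ceiling for nine outcomes under that assumption.

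**3. Sub-study 1, the plan's own figure.** Inputs from section 2.4.4: 25 classes per group (J = 50), n = 18 pupils per class, ICC = 0.046, three covariates, power 0.80, two-sided 0.05. No R² is given, so R² = 0 is assumed.

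SE = √[0.046/(0.25 × 50) + 0.954/(0.25 × 50 × 18)] = 0.0890. With df = 50 − 3 − 2 = 45, the multiplier is 2.014 + 0.850 = 2.864. The minimum detectable effect size (MDES) is 2.864 × 0.0890 = 0.255, with interval 0.255 ± 2.014 × 0.0890 = 0.076 to 0.434. Both match the stated figures, so the calculation is for one outcome at 0.05.

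**4. Sub-study 1, error for a claim resting on any of three.** Section 2.4.5 counts only differences favouring the intervention group, so the relevant error per test is 0.025.
- Independent: 1 − 0.975^3 = 0.073
- Simulated: 6.2–6.3% at r = 0.5, 5.4–5.5% at r = 0.7, 4.2% at r = 0.9

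This is about 4 to 7% against a nominal 2.5%.

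**5. Cost of Holm in Sub-study 1.** Holm's strictest step for three outcomes is 0.05/3 = 0.0167. The same formula gives:

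| Classes per group | MDES at 0.05 | MDES at 0.0167 |
|---|---|---|
| 25 | 0.255 | 0.297 |
| 75 (target, section 2.2; 18 pupils per class assumed) | 0.145 | 0.168 |

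**The case against.** Multiplicity rules are often left to a statistical analysis plan that is not shown here, and a 0.05 threshold does not by itself rule out adjusted p-values. This would carry weight if the article were merely silent. It is not: section 2.5.2 itself makes the whole list primary and section 2.5.5 sets the threshold, so a later plan would have to override this text. The repeated entry and the nesting of MPA in MVPA are visible in the article whatever another document says.

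The 37% assumes independence, which these outcomes do not have. That objection stands, and 37% should be read only as a ceiling.

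For Sub-study 1 the opposing case largely succeeds. Three stronger readings are tempting, and the documents do not support them:
- **That the false-positive rate for Hypothesis 1 is 14%, far above 5%.** The figure 1 − 0.95^3 = 0.143 counts errors in both directions, while section 2.4.5 claims an effect only for better development in the intervention group. Section 2.4.5 also has a separate model and a separate effect for each outcome, and on that reading each test keeps its stated error and power.
- **That requiring all three outcomes cuts power to 0.8^3 = 51%.** This holds only for 25 classes per group, at d = 0.255 and with independent outcomes. At the target of 75 classes per group, power at d = 0.255 is 0.9985 per outcome, and 0.9985^3 ≈ 0.996 jointly.
- **That the rate is 26% because SM has four regulation types.** The figure 1 − 0.95^6 = 0.265 assumes four SM tests, but section 2.4.5 specifies one SM model.

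A reader might also want MVPA as the sole primary PA outcome. Hypothesis 2 also concerns patterns of movement, which MVPA alone would leave without a primary test.

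**Conclusion.** The point holds for Sub-study 2. As written, nine distinct outcomes are co-equal primaries under one hypothesis, two of them overlap, one entry is duplicated, and each is tested at an unadjusted 0.05. The chance of at least one false-positive primary PA finding is about 12 to 27% at assumed equal correlations of 0.9 to 0.5, and at most 37% if the tests are independent. These figures assume no true difference on any outcome and normal test statistics. The correlations are assumptions, but the rate exceeds 5% at every value tried.

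For Sub-study 1 only a minor point remains: the joint wording of Hypothesis 1 and the outcome-by-outcome models should be brought into line. The sub-study designs are not in question.

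**What to change.** **Sub-study 2**
- Correct the repeated activity type in section 2.5.2.
- Keep only one of MPA and MVPA in the primary set, or redefine them so that they do not overlap.
- Control the family-wise error across the primary PA outcomes in one of two ways: apply Holm to all of them, or name in advance one intensity outcome and one movement-pattern outcome to match the two parts of Hypothesis 2 and make the rest secondary. Two named outcomes at 0.05 each would still give 1 − 0.95² = 9.75% if independent, so Holm should be applied to the pair unless both are required for Hypothesis 2.

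**Sub-study 1**
- State that effects are claimed separately for FL, CCL and SM.
- If a claim for the program as a whole will rest on any one of them, report Holm-adjusted p-values across the three.

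**Cost.** The changes need rewording and adjusted p-values, with no new data. Section 2.3 says that data were not accessed before the protocol was submitted. The price is somewhat lower power per outcome. In Sub-study 1, at Holm's strictest step, the MDES rises from 0.145 to 0.168 at 75 classes per group. If only 25 classes per group are reached it rises from 0.255 to 0.297, so the plan's reassurance about under-recruitment would have to be restated. In Sub-study 2, Holm across nine outcomes starts at 0.05/9 = 0.0056; naming two outcomes raises that first step to 0.05/2 = 0.025.
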